## Abstract

**Background:**

A number of problems involving the temporomandibular joint (TMJ) and associated structures can lead to temporomandibular disorder (TMD). The aim of the proposed study is to assess the effect of low-level laser therapy on occlusal contacts, mandibular movements, electromyography activity in the muscles of mastication and pain in adolescents with TMD.

**Methods/Design:**

A randomized, controlled, double-blind, clinical trial will be carried out involving 85 male and female adolescents between 15 and 18 years of age. The research diagnostic criteria for TMD will be used to assess all individuals who agree to participate. All participants will be submitted to a clinical examination and electromyographic analysis of the masseter muscles and anterior bundle of the temporal muscles bilaterally, to determine TMD. Based on the clinical findings, the participants will be classified as having or not having TMD. Those with TMD will be divided into four groups, three of which will receive low-level laser therapy and one of which will receive a placebo treatment. The treatments will involve the TMJ region alone, the masseter and temporal muscles alone, or both these regions together. The data will be submitted to descriptive statistical analysis. The chi-square test and Fisher’s exact test will be used to determine associations among the categorical variables. The Student’s *t* test and analysis of variance will be used for the comparison of mean electromyographic signals. Pearson’s correlation coefficients will be calculated for the analysis of correlations among the continuous variables.

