### Procedures

As the proposed study constitutes a randomized clinical trial, the recommendations of the Consolidated Standards of Reporting Trials (CONSORT) [26] will be followed to allow greater transparency and enhance the quality of the findings. The subjects will be allocated to five groups, as delineated in Table 1.

**Table 1 T1:** Summary of experimental conditions

**Group**	**TMD**	**Laser application site**	**Therapeutic intervention**
I	Absent	—	Control group
II	Present	TMJ	LLLT
III	Present	Muscles of mastication	LLLT
IV	Present	TMJ and muscles of mastication	LLLT
V	Present	TMJ and muscles of mastication	Placebo

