#### Application of low-level laser therapy

A gallium-aluminum-arsenide laser (Twin Flex Evolution®, MM Optics) will be employed for the LLLT and placebo treatment. The sessions will be held in a reserved, noise-free room. The volunteer will be positioned with the Frankfurt plane parallel to the ground. The active tip of the laser will be covered in disposable plastic wrap to avoid cross-contamination and for hygiene reasons. The operator will wear suitable protective clothing. The skin at the site to be irradiated will have previously been cleaned with 70% alcohol. Both the operator and volunteer will use protective eyewear.

Two sessions of LLLT or placebo treatment will be carried out over six weeks (a total of 12 sessions). The device will be calibrated with a wavelength of 780 nm, an energy density of 25 J/cm^2^, a power of 50 mW, and a power density of 1.25 W/cm^2^. The exposure time will be 20 s per point, resulting in a total energy of 1 J per point. The spot application method will be used: the laser will have a conventional tip in contact with the skin and will cover an area of 0.04 cm^2^, as suggested by Venezian *et al*. [24] and Carvalho *et al*. [14]. Three of the four groups with TMD will receive LLLT and one will receive a placebo treatment:

1. TMJ region: five points around the TMJ [7,13], totaling 5 J.

2. Masseter and temporal muscles: three points on the masseter (upper, middle and lower) and one point on the anterior temporal [24], totaling 4 J.

3. Mixed application: TMJ and muscles of mastication [12,14], resulting in 9 J.

4. Placebo treatment: the same equipment will be used with a pen that emits a red guide light and a warning sound, but without the emission of a laser beam.

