### Sample size calculation

Based on data from the literature [24], using the EMG signal of the masseter muscles, and following LLLT as the basis, with mean values of 13.4 (standard deviation: 2.8) and 11.9 (standard deviation: 1.9) individuals per group, for the experimental study and comparison of means with equal samples (hypothesis test), considering a 5% level of significance (*P* < 0.05) and 80% test power, the sample size was determined to be 15 individuals per group, using the DINAM 1.0 program [32].

Seventeen individuals will be selected for each group to compensate for possible losses.

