#### Organization and statistical treatment of data

The data will be tabulated and treated using the SPSS 12.0 program for Windows and will be submitted to descriptive statistical analysis. The chi-square test and Fisher’s exact test will be used to determine associations among the categorical variables. The Student’s *t* test for paired data will be used to analyze the averages of electromyographic and occlusal contacts before and after treatment. The Student’s *t* test and analysis of variance will be used to compare mean electromyographic signals and occlusal contacts between different groups. For data that are not normally distributed, the differences before and after treatment in the same group and between groups will also be analyzed, using the Mann–Whitney and Wilcoxon paired tests. Pearson’s correlation coefficients will be calculated for the analysis of correlations among the continuous variables. The level of significance will be set to 5% (*P* < 0.05).

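### Groups II–V form a complete 2×2 of laser site, but the plan names no site effect, interaction or baseline term; one prespecified model could add them beside the active–placebo contrasts

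*Protocol article*

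**What the plan says.** The abstract describes the TMD arms: "Those with TMD will be divided into four groups, three of which will receive low-level laser therapy and one of which will receive a placebo". Of the active arms it says "The treatments will involve the TMJ region alone, the masseter and temporal muscles alone, or both these regions together". Table 1 (Procedures) lists Group II as laser at the TMJ, III at the muscles of mastication, IV at both, and V as placebo at both. Group I has no TMD. It is counted in the statement that "The subjects will be allocated to five groups, as delineated in Table 1", but membership depends on diagnosis and cannot be randomised.

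Under Application of low-level laser therapy, the TMJ arm totals 5 J and the muscle arm 4 J. The combined arm is given as "Mixed application: TMJ and muscles of mastication [12,14], resulting in 9 J".

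The Sample size calculation is framed as a "comparison of means with equal samples (hypothesis test"), "with mean values of 13.4 (standard deviation: 2.8) and 11.9 (standard deviation: 1.9) individuals per group", and arrives at 15 per group, raised to 17 for losses.

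Under Organization and statistical treatment of data, the paired t test handles before–after change. Between groups, the t test and "analysis of variance will be used to compare mean electromyographic signals and occlusal contacts between different groups"; Mann–Whitney and Wilcoxon tests cover non-normal data. That section does not state the form of the ANOVA. It names no site effect, interaction or baseline covariate, and does not restrict any comparison to the randomised arms.

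**The concern.** Groups II, III, IV and V are the four cells of a balanced 2×2, and the combined energy is exactly the sum of the two single-site energies (5 + 4 = 9 J). Such a layout can show what laser at each site contributes and whether the two together do more or less than their sum. The analysis as described is group against group. A single-site arm set against placebo uses two of the four arms, 34 of the 68 planned TMD participants. A main effect for that site uses all 68.

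Baseline EMG and baseline occlusal contacts are collected, but no between-group comparison is said to adjust for them. In a trial this small, the unused precision matters. The combination question would otherwise have to be pieced together from pairwise p-values.

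**Working it through.** **Inputs (Sample size calculation).** Means 13.4 and 11.9, so Δ = 1.5. SDs 2.8 and 1.9, so s = √[(2.8² + 1.9²)/2] = √5.725 = 2.393 and d = 1.5/2.393 = 0.627. The level is 5%; sidedness is not stated, so two-sided is assumed. There are n = 15 per arm, or 17 before losses.

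**The plan's own figure.** n per group = 2s²(1.960 + 0.842)²/Δ² = 2 × 5.725 × 7.849/2.25 = 39.9, so 40 (41 with the t distribution); one-sided gives 32. The stated 15 is not reproduced by a comparison of two independent groups.

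**Standard errors.**
- Single-site arm v placebo: s√(2/n) = 0.874 at n = 15, 0.821 at n = 17.
- Site main effect (two arms v two arms): s√(1/n) = 0.618, 0.580.
- Interaction: 2s/√n = 1.236, 1.161.

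The variance ratio of the first to the second is (2/n)/(1/n) = 2.

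**Power for Δ = 1.5 with no interaction (noncentral t).**

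| | 15 per arm | 17 per arm |
|---|---|---|
| Single-site arm v placebo | 38% | 43% |
| Site main effect | 67% | 72% |

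Without baseline adjustment, 80% for a main effect needs about 20–21 per arm, against 40–41 for a pairwise contrast.

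**When the sites are not additive.** Let each site alone give 1.5 and let I be the interaction. The main effect is then [1.5 + (1.5 + I)]/2 = 1.5 + I/2. If the second site adds nothing, I = −1.5 and the main effect is 0.75. Power is then 22% (n = 15) or 25% (n = 17), below the pairwise figures. The two approaches break even roughly where 1.5 + I/2 = 1.5/√2 = 1.061, so I = −0.88. At that point the second site delivers (1.5 − 0.88)/1.5 = 41% of its stand-alone effect.

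**Can the trial tell which case it is in?** Power to detect an interaction of 1.5 is 22% (n = 15) or 25% (n = 17). The 95% CI half-width for the interaction is 2.003 × 1.236 = 2.48 or 1.998 × 1.161 = 2.32, wider than the planned effect itself.

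**Baseline adjustment.** The baseline–outcome correlation r is not in the document, so a range is assumed. The residual SD is s√(1 − r²), a factor of 0.954, 0.866 or 0.714 for r = 0.3, 0.5 or 0.7. At 15 per arm and under additivity, power for a site main effect is about 71%, 79% and 92%. The same model also helps the active–placebo contrasts: SE = 0.874 times the factor = 0.833, 0.757, 0.624, with power about 42%, 50% and 66% on 55 error degrees of freedom.

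**The case against.** The strongest reply is that nothing here is wrong. The stated aim is the effect of laser therapy in general, and no site-specific or additivity hypothesis is declared. Asking whether each regimen beats placebo is a proper question, and pairwise contrasts answer it without assuming additivity. That stands, and it is why those contrasts should stay.

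A reader might infer that the plan commits to a one-way ANOVA. It does not: the form is unstated, a factorial ANOVA is not excluded, and model terms may be set out in a fuller document that is not shown. Group-against-group comparison is only the natural reading of the named tests and of the two-mean sample size.

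A reader might also infer that half the data are simply thrown away, or that a factorial analysis rescues the sample size. The document supports neither. The gain depends on rough additivity, about which the article gives no evidence, and it reverses under strong sub-additivity. Falling back on simple effects when the interaction looks material is not a workable safeguard, because the interaction is estimated too imprecisely to guide that choice.

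Finally, sham is described only for the placebo arm. The article does not say whether Groups II and III receive sham at the untreated site. If they do not, the 2×2 is complete in treatment but not necessarily in blinding. That would affect the pairwise contrasts with placebo as well.

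**Conclusion.** The point holds as a cheap improvement, not as an error in the plan. Groups II–V are a complete 2×2, and the described analysis names no site effect, interaction or baseline term. Halving the variance of each site's effect is exact arithmetic. The power gains (38% to 67%, or 43% to 72%) rest on approximate additivity, d = 0.627 and a two-sided 5% test. The gain from baseline adjustment does not need additivity, but its size depends on a correlation that the document does not give. The inconsistency between 15 per group and the stated inputs (about 40) is a separate matter that this change leaves unrepaired.

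**What to change.** In Organization and statistical treatment of data, prespecify one linear model restricted to Groups II–V, leaving out the non-randomised Group I, with the baseline value as a covariate and terms for TMJ laser, muscle laser and their interaction.

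- Keep the three active–placebo differences from this model as the regimen comparisons.
- As prespecified supplementary estimates, report each site's main effect, (II + IV) v (III + V) for the TMJ and (III + IV) v (II + V) for the muscles, averaged equally over the other site, and the interaction, all with 95% CIs.
- Do not choose between the two sets by an interaction test, and state that a non-significant interaction is not evidence of additivity.

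The cost is one model and a few lines of text, with no extra participants, visits or measurements. The downside is that the main effects average over the other site's treatment. They mislead about a single-site regimen if the sites interact strongly, and this trial has little power to detect that.

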**Trial registration:**

The protocol for this study has been submitted to Clinical Trials – registration number (NCT01846000).

## Background

Temporomandibular disorder (TMD) is a term used for a large number of clinical signs and symptoms that affect the muscles of mastication, the temporomandibular joint (TMJ) and associated structures [1-9]. Postural and occlusal abnormalities, parafunctional habits, and psychological factors can lead to TMD [2,4,5,8]. Orofacial pain is the most common complaint among individuals with this condition [2,4,5]. Other symptoms include sensitivity in the muscles of the head and neck region (including the muscles of mastication), pain in one or both TMJs, limited mandibular movements, joint noises, [1-7,10-14] headache, [1-6,10] dizziness, hearing loss and ringing in the ears [2-5]. The presence of symptoms can affect the quality of life and the social life of the patient.

The stomatognathic system includes the maxilla, mandible, teeth, TMJs, and muscles of mastication and is directly related to the cervical spine. The neuromuscular influences of the neck region and the function of mastication actively participate in mandibular movements and the positioning of the cervical spine. Balance and synchrony between the anterior and posterior muscles of the head and neck are needed to establish the resting position of the mandible [4,5].

Alterations in postural balance result in a change in electrical activity in the muscles of mastication, which can be determined using electromyography (EMG) [4]. Electromyographic analysis of these muscles can provide information regarding physiological abnormalities in the stomatognathic system of individuals with TMD in an effort to clarify the relationship between electrical activity and the mechanical response of the muscles [15,16].

Occlusal interferences are related to signs and symptoms of TMD [17,18], can affect chewing function and can lead to asymmetry in the stomatognathic system. Studies involving individuals with adequate occlusion (absence of dysfunction) have demonstrated that mastication occurs with symmetrical activity between the right and left masseter and temporal muscles. However, the muscle contraction pattern is altered and asymmetrical in individuals with occlusal interferences, as demonstrated by EMG during mastication [17].

Low-level laser therapy (LLLT) is a low-cost noninvasive treatment that has proven to be beneficial in the treatment of pain related to TMD [1-3,6,11,19-22]. The therapeutic effects of LLLT include the modulation of inflammatory processes, analgesia and cellular activity [1-3,6,7,11-13,19-25]. Despite the reported benefits [1-3,6,11,20-22], few studies have analyzed the effects of LLLT administered to adolescents with a diagnosis of TMD [1-3,6,7,11-13,20-25].

The aim of the proposed study is to assess the effect of LLLT on pain, occlusal contacts, mandibular movements, and electromyography activity in the masseter and temporal muscles in adolescents with TMD.

## Methods/Design

A randomized, controlled, double-blind, clinical trial will be carried out. The protocol for this study received approval from the Human Research Ethics Committee of the *Universidade Nove de Julho* (São Paulo, Brazil) under process number 40455. The legal guardians of the participants will sign a statement of informed consent authorizing participation in the study. Figure 1 summarizes the trial design.

**Figure 1 F1:**
[figure not shown]
Flow chart of experimental design.

### Subjects

Male and female adolescents enrolled at the clinics of the Master’s program in Rehabilitation Sciences of the *Universidade Nove de Julho* (Vergueiro Campus, São Paulo, Brazil) will be evaluated.

#### Inclusion criteria

Individuals aged 15 to 18 years with a diagnosis of TMD and a signed statement of informed consent will be included in the study.

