#### Diagnosis of temporomandibular disorder

Prior to any intervention, participants eligible for the study will be diagnosed with TMD, using the Research Diagnostic Criteria for Temporomandibular Disorders (RDC/TMD) questionnaire. Moreover, a specific clinical examination will be carried out by a single, previously trained, examiner. This examination will consist of palpation of the temporal, masseter, digastric and medial pterygoid muscles, palpation of the TMJs and an analysis of the mandible with the aid of a digital caliper to measure vertical and horizontal movements and a stethoscope to assess joint noises. The following will also be investigated: frequent headache, facial pain, fatigue, and difficulty during mastication, bruxism (clenching or grinding of teeth), psychological status, and parafunctional habits.

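### Any TMD is eligible and the laser arms are defined by joint or muscle site, but the stated between-arm analysis ignores the joint/muscle findings recorded at baseline

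*Protocol article*

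**What the plan says.** All places are in the protocol article.

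- **Background** describes TMD as covering "a large number of clinical signs and symptoms that affect the muscles of mastication, the temporomandibular joint (TMJ) and associated structures", so muscle and joint conditions fall under one label.
- **Inclusion criteria** set this entry rule: "Individuals aged 15 to 18 years with a diagnosis of TMD and a signed statement of informed consent will be included in the study". Neither these nor the Exclusion criteria restrict the type of TMD.
- **Methods/Design**: "A randomized, controlled, double-blind, clinical trial will be carried out".
- **Procedures and Table 1**: "The subjects will be allocated to five groups, as delineated in Table 1". Group I has no TMD. Groups II, III and IV have TMD and receive laser to the TMJ, to the muscles of mastication, or to both. Group V has TMD and receives placebo.
- **Application of low-level laser therapy** gives total energies of 5 J, 4 J and 9 J for the joint, muscle and combined applications.
- **Diagnosis of temporomandibular disorder**: before any intervention, "participants eligible for the study will be diagnosed with TMD, using the Research Diagnostic Criteria for Temporomandibular Disorders (RDC/TMD) questionnaire". The clinical examination includes "palpation of the temporal, masseter, digastric and medial pterygoid muscles, palpation of the TMJs". The use that the Abstract states for the clinical findings is to classify participants as having TMD or not.
- **Organization and statistical treatment of data** compares groups by Student's t test and analysis of variance, or by a rank test if the data are not normal. It names no baseline factor.

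**The concern.** Site of irradiation is the factor that separates the laser arms, so the affected structure is an obvious candidate to modify the effect or to predict outcome. A patient with muscle disease only can be placed in the joint arm, and a patient with joint disease in the muscle arm.

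Two things are at stake:

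- **Chance imbalance and precision.** In arms of 17, the share of joint-type patients can differ noticeably between arms. If that share is related to outcome, the observed difference between arms moves with it, and unexplained variation widens every confidence interval.
- **Interpretation.** Each single-site arm estimates an average over patients irradiated at the affected structure and patients irradiated elsewhere. Without results by category, the reader cannot tell whether the site effect depends on the structure affected.

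The information needed is already collected before treatment, but the stated analysis does not use it.

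**Working it through.** **Inputs from the article.** There are 17 per group after allowance for losses, and 5 × 17 = 85 agrees with the stated total. The TMD groups hold 4 × 17 = 68. The planning values in Sample size calculation are means of 13.4 and 11.9 (difference 1.5) and SDs of 2.8 and 1.9, so the pooled variance is (2.8² + 1.9²)/2 = 5.725 and the pooled SD is 2.393.

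**Assumptions.** The article does not give the share p of patients with joint involvement, so p = 0.3, 0.5 and 0.7 are used. It does not describe the allocation method, so simple randomisation is assumed.

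**1. Size of chance imbalance.** The joint-type counts in two arms are independent Binomial(17, p). The expected difference in share is 0, with SD √(2p(1−p)/17):

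| p | SD of difference | P(difference ≥ 4 patients, i.e. 24 points) |
|---|---|---|
| 0.3 or 0.7 | √(0.42/17) = 0.157 | 0.189 |
| 0.5 | √(0.50/17) = 0.171 | 0.229 |

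The probability that at least one of the three pairs of laser arms differs by 4 or more patients is 0.39 to 0.45 (simulation).

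**2. What an imbalance of 4 patients does to one comparison.** Suppose joint and muscle patients differ by g units in mean outcome. A gap of 4 out of 17 then shifts the difference between the arms by (4/17) × g:

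- g = 1.5: 0.235 × 1.5 = 0.35
- g = 3.0: 0.235 × 3.0 = 0.71

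Against the planned difference of 1.5, these are 24% and 47%. The values of g are illustrative.

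**3. Loss of precision.** Take the pooled SD as the SD within each category, with p = 0.5. The unadjusted variance is then 5.725 + g²/4:

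- g = 1.5: 5.725 + 0.5625 = 6.29, or 10% more. The standard error √(2 × variance/17) rises from 0.82 to 0.86.
- g = 3.0: 5.725 + 2.25 = 7.98, or 39% more. The standard error rises to 0.97.

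**4. Validity of the unadjusted test.** With simple randomisation, 17 per arm, p = 0.5 and g = 0, 1.5 and 3.0, the simulated type I error of the unadjusted two-sample t test was 5.1%, 4.9% and 5.0%. The mean bias was about 0.

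**5. Dilution.** If the laser acted only on the affected structure, and every patient had disease in only one structure, a single-site arm would show the effect multiplied by its on-target share. With half on target, the planned 1.5 becomes 0.75. This is an extreme case, because a patient with both structures affected is on target in every laser arm.

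**6. Size of the categories.** At a 30% share, the smaller category has 0.3 × 68 = 20.4 patients, about 5 per arm.

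**The case against.** **A reader might infer that the site comparison is confounded with case mix.** The article does not support this. The TMD groups are described as randomised, so case mix is independent of arm in expectation, and step 4 shows an unbiased comparison with type I error near 5%. An imbalance by chance is already allowed for in the test. This objection stands in full. What remains is precision and interpretation.

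**A reader might infer that the laser arms differ in nothing but site.** They also differ in total energy (5, 4 and 9 J). That difference is tied to site by design, and neither randomisation nor adjustment for diagnosis removes it.

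**A reader might infer that allocation is known to be unstratified.** It is not known. The article does not describe the allocation method, the flow chart is not shown, and a condensed article may leave stratification and covariates to the full protocol or analysis plan. Silence on allocation cannot carry the point. It rests on what is stated: open eligibility, arms defined by site, and between-group tests with no baseline factor.

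**Broad eligibility is legitimate.** The stated aim concerns adolescents with TMD, not subtypes, and an average over the enrolled mix answers that. The Background also treats joint and muscles as one linked system, and EMG and palpation pain are measured on muscle whatever the diagnosis. This stands: no passage establishes that laser works only on the affected structure, so the dilution figure is illustrative.

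**The imbalance figures would apply to any binary baseline factor of similar frequency.** This is true. What sets this factor apart is that it corresponds directly to the experimental factor and is already recorded.

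**Conclusion.** The point holds as an improvement to the stated analysis. It is not a flaw that invalidates the comparison. Any TMD is admitted, the laser arms are defined by joint, muscle or both, and the stated between-group tests leave out the joint/muscle findings recorded before treatment. Two given arms of 17 would differ by at least 4 joint-type patients with probability about 0.19 to 0.23. This rests on an assumed joint share of 30% to 70% and simple randomisation, and stratified allocation would make such gaps rarer. How far an imbalance matters depends on how strongly the category predicts outcome, which the article does not state. The results would also average over patients whose affected structure may not be the one irradiated, and the plan provides no view of whether the effect depends on it.

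**What to change.** 1. In **Organization and statistical treatment of data**, replace the unadjusted between-arm comparison of Groups II to V with an ANCOVA that includes the baseline RDC/TMD category (muscle only versus joint involvement) as a covariate. Group I has no TMD and stays outside this model.
2. Report arm effects by category descriptively only, without tests, since the smaller category may have about 5 patients per arm.
3. Trial status says that recruitment is under way. For patients not yet randomised, use the same two categories as a randomisation stratum in **Procedures**, if the full protocol does not already do so. For those already randomised, the covariate alone applies.

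**Cost.** One model degree of freedom (residual 64 to 63 with 68 patients and four arms) and a second allocation list. No new measurement, visit or patient is needed. The gain is better balance and, if the category predicts outcome, better precision. The change does not remove dilution, because each single-site arm may still contain patients whose affected structure is not irradiated, and it does not separate site from total energy.
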